### Data collection

Figure 1 provides an outline of the RCT. At enrollment, the research assistant will collect baseline demographics data and complete the Peds-QL and EQ-5D-YL with the child and/or caregiver via a face to face meeting or phone review, whichever method is preferred by the caregiver. As the EQ-5D-Y questionnaire is designed for completion by children aged 8–15, we will attempt to obtain both child and parent-proxy completed measures for children in this age bracket.

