### Sample size and statistical power

Accepting an alpha risk of < 0.05, a beta risk of < 0.2 and assuming a 10% risk of dropout during follow-up, *n* = 26 patients in each group is required to identify a statistically significant reduction of at least one medical appointment between groups. The sample size determination was not reliant on the standard deviation as a sample size formula input due to the number of medical appointments being considered a count variable [22].

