### Statistical analyses

To account for clustering at the hospital level and repeated measures over time, multivariable mixed-effects regression models will be built to estimate the interventional effect of health related quality of life and patient experiences between and within groups. Multivariable mixed-effects regression models were chosen to to minimise bias due to group imbalance and its effects on the internal validity of the study [23]. For each model building process, variables found to be significantly associated with the outcome measure in the univariable analysis at the 10% level will be retained in the final model. As the primary predictor of interest, intervention effect will be forced into the multivariable model. Continuous outcome measures will be analysed using linear regression models. For dichotomous measures, the analysis will be by binary logistic regression, while multinomial logistic regression will be used to analyse nominal measures. Model diagnostics will be conducted on all models to ascertain their appropriateness. Each model will be tested for violations of model assumptions, the existence of influential points and goodness of fit. Tests for all outcomes will be two-tailed, with levels of statistical significance set at 5%. To assess the missingness mechanism, Little’s test for missing completely at random (MCAR) will be used.

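### For PedsQL and EQ-5D-Y the model-building rule forces in only an undefined intervention effect; read literally, it would estimate about half of the follow-up difference

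*Protocol article*

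**What the plan says.** Under Data collection, the protocol article sets two time points for the quality-of-life instruments. The first is "At enrollment, the research assistant will collect baseline demographics data and complete the Peds-QL and EQ-5D-YL". The second is within 7 days of the child's last medical specialist appointment. AFEQ and Measure of Processes of Care are listed only at the second. Under Randomisation, the arm is assigned after enrolment.

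Under Statistical analyses, the opening sentence reads in part: "repeated measures over time, multivariable mixed-effects regression models will be built to estimate the interventional effect of health related quality of life". The same sentence also covers hospital clustering and the experience measures, and asks for effects both between and within the arms. Two rules then govern what enters each model:

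- The rule for candidate covariates is: "variables found to be significantly associated with the outcome measure in the univariable analysis at the 10% level will be retained in the final model".
- The rule for the treatment term is: "As the primary predictor of interest, intervention effect will be forced into the multivariable model".

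The section names no time term, no arm-by-time term and no adjustment for the enrolment score. It does not say whether the intervention effect is a main effect of arm or an interaction with time, nor whether the enrolment score is an outcome row or a covariate.

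**The concern.** The enrolment score is taken before either pathway starts, so the pathway cannot have affected it. With only two visits, there are repeated measures over time only if the enrolment score is itself an outcome row; as a covariate, it would leave one outcome per child. An analyst who follows the text literally therefore stacks both visits, forces in arm, and adds whatever passes the screen. A univariable screen of variables does not naturally supply an arm-by-time product, and it could drop time as well.

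In that model the arm coefficient averages a pre-treatment difference, expected to be zero, with the follow-up difference. The hypothesis under Aims is that quality of life is comparable in the two pathways. An estimate pulled halfway to zero favours that conclusion: a real harm would be reported at about half its size and would often be non-significant. Adding a comparability margin would not repair it, because the interval would be centred on the wrong quantity.

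**Working it through.** **The plan's own figure.** The only sample-size figure is 26 per group, for a reduction of one medical appointment, with "a beta risk of < 0.2" and "assuming a 10% risk of dropout during follow-up". No control-arm mean is given, so it cannot be reproduced from the stated inputs alone. If means of 2 and 1 appointments are assumed, the square-root rule gives 4/(√2 − √1)² = 23.3, and 23.3/0.9 = 25.9, i.e. 26. The figure says nothing about quality of life. Only the number of children is used below.

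**Inputs**

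- From the document: 26 per group and 10% dropout, so 26 × 0.9 = 23.4, taken as n = 23 per arm; two-sided 5%; two quality-of-life visits; arm assigned after enrolment.
- Assumed, because the document gives no quality-of-life effect, SD or correlation: SD 1 at both visits; true follow-up difference d = 0.8 SD; correlation r between visits of 0.3 to 0.7; enrolment scores taken before allocation, so that the expected baseline difference is 0.

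**Expected value.** With complete pairs, the arm coefficient of a random-intercept model without arm-by-time is the difference between arms in the child's mean over the two visits:

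(0 + d)/2 = d/2, so 0.8 SD becomes 0.40 SD.

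Adding time as a main effect does not change this. The halving does not depend on d or r.

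**Standard errors**

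- Arm main effect over both visits: √[(2/n)(1 + r)/2]
- Plain arm-by-time (difference in change): √[(2/n) × 2(1 − r)]
- Follow-up adjusted for baseline: √[(2/n)(1 − r²)]

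At r = 0.5 and n = 23, the first and third are both √[(2/23) × 0.75] = 0.255. The ratios of effect to SE are 0.40/0.255 = 1.57 and 0.80/0.255 = 3.13, so the test statistic is exactly halved. Power is Φ(ratio − 1.96):

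| r | Arm main effect (estimates 0.40) | Plain arm-by-time (estimates 0.80) | Baseline-adjusted (estimates 0.80) |
|---|---|---|---|
| 0.3 | 39% | 63% | 81% |
| 0.5 | 35% | 77% | 88% |
| 0.7 | 31% | 94% | 97% |

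For a smaller true difference of 0.5 SD at r = 0.5, the three figures are 16%, 40% and 50%.

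**Check by fitted mixed models.** Simulation used 26 per arm, r = 0.5, true difference 0.8 SD and 10% of follow-ups missing (200 runs). The arm coefficient with arm and time in the model averaged 0.38 (36% of runs significant). The plain arm-by-time coefficient averaged 0.77 (74%). The arm-by-time coefficient with baseline means constrained equal averaged 0.78 (87%). Without dropout the first was 0.43; with 30% dropout it was 0.32. Dropout pushes it below half because children lost to follow-up contribute only their enrolment row, where there is no effect.

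**The case against.** The strongest reply is that the article does not fix the model described above. It never calls the forced term a main effect. It aims at effects between and within arms over time, which points towards a group-by-time contrast, since an arm-only model yields no within-arm estimate. The screen can be read as applying to candidate covariates only, with time treated as model structure. The section also says the models were chosen to limit bias from imbalance between groups, which is compatible with adjusting for the enrolment score. If that score were a screened candidate, it would usually survive: by a Fisher-z approximation with 46 children, a correlation of 0.5 passes the 10% level about 97% of the time, and 0.3 about 65%. Coding of time and baseline is often left to an analysis plan, and none is shown.

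Much of this stands. A reader might infer that the protocol commits the trial to a halved quality-of-life effect; the text does not support that. The reply also limits the scope. AFEQ and Measure of Processes of Care are collected once, so no averaging over visits can occur. Appointment counts and costs, which carry the sample size and the primary outcome named in the Discussion, are untouched. The cost-consequence analysis separately summarises differences between the models of care with 95% confidence intervals, so this regression is not the only evidence on quality of life.

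What does not stand is that this is only missing detail. The article states a rule for what is forced and what is screened, and that rule permits the diluted estimate. Naming between- and within-arm effects supplies no model term. Baseline adjustment that depends on a screen, at 65% in the weaker case, is not guaranteed.

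**Conclusion.** The point holds conditionally, for PedsQL and EQ-5D-Y only. The stated rule leaves the intervention effect undefined and guarantees neither baseline adjustment nor an arm-by-time term. Under the literal reading, the reported coefficient is about half the follow-up difference, and somewhat less with dropout. The halving follows from the design. The power figures (31% to 39%, against 81% to 97% with baseline adjustment or 63% to 94% with plain arm-by-time) rest on the assumed 0.8 SD, r of 0.3 to 0.7 and 23 per arm.

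A reader might go further and conclude that the trial's main findings are at risk, or that within-arm tests will be offered as proof of a pathway effect. The document supports neither. It only names within-arm estimates alongside the between-arm ones, and a within-arm change measures change over time, not the effect of the pathway. The correction should be made because the possible error lies in the direction of the trial's own hypothesis and is cheap to exclude.

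**What to change.** In Statistical analyses, define the intervention effect on PedsQL and EQ-5D-Y as the between-arm difference at follow-up, and name one way of estimating it:

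- regress the follow-up score on arm, with the enrolment score always included as a covariate; or
- fit a mixed model that always includes time and arm-by-time, with baseline means constrained equal, and report the arm-by-time coefficient.

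State that these terms are exempt from the 10% screen, and that within-arm changes are descriptive only.

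If the sponsor already intended one of these, the same wording records it. The cost is one or two sentences and one or two extra fixed model terms. No further data or children are needed, because the enrolment score is already collected.

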## Methods

### Aims

This aim of this study is to determine if an allied health first-contact model of care reduces health service use and costs without compromising patient quality of life or satisfaction when compared to traditional medical first-contact models of care in the assessment of ASD in children. We hypothesize that an allied health first-contact model of care reduces healthcare use and costs; and results in comparable patient quality of life and satisfaction with care, when compared to a traditional medical first-contact model of care.

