## Discussion

This randomised controlled trial will investigate the impacts of an allied health first contact model for the assessment of paediatric ASD on health service use and costs, family out of pocket costs, patient quality of life, patient satisfaction with care and patient waiting times. It is anticipated that the allied health first contact model will result in the reduction of at least one paediatrician appointment on average per child without compromising on patient quality of life and satisfaction, when compared to the traditional medical specialist first contact model.

To our knowledge, this will be the first randomised controlled trial of an allied health first contact model for the assessment of children with ASD internationally. This is a rigorous study design that will minimise the likelihood of bias in our findings. Nonetheless, some limitations exist. The type of families that consent to be involved in a research study may differ from families that choose not to be involved; this may introduce a selection bias that could limit the generalisability of our conclusions. Data collected from families on their out of pocket costs will be obtained at key time points throughout the trial, but may be subject to the effects of recall bias when asking caregivers to record costs occurring in the past. Data collected on health service use and costs, the primary outcome, will be obtained from administrative databases and are therefore expected to be comprehensive and accurate. However, this will be limited to emergency department presentations, hospital admissions, as well as allied health and specialist appointments that are provided by the health service. Data on primary or community-based care and pharmaceutical use will not be captured within this study.

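### Quality of life and satisfaction are hypothesised to be comparable, but the plan fixes only tests of difference and no threshold, so no planned result can confirm that part of the hypothesis

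*Protocol article*

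**What the plan says.** All references are to the protocol article.

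- **Aims.** Service use and costs should fall "without compromising patient quality of life or satisfaction when compared to traditional medical first-contact models of care". The hypothesis adds that the new model "results in comparable patient quality of life and satisfaction with care, when compared to a traditional medical first-contact model of care".
- **Discussion.** At least one paediatrician appointment fewer per child is anticipated, "without compromising on patient quality of life and satisfaction". The closing paragraphs say that, if the hypotheses prove correct, resources may be freed while quality of life and experience of care are maintained or possibly improved, and that this may inform wider adoption.
- **Statistical analyses, models.** For these outcomes, "multivariable mixed-effects regression models will be built to estimate the interventional effect of health related quality of life and patient experiences". The section then sets the test for everything: "Tests for all outcomes will be two-tailed, with levels of statistical significance set at 5" per cent.
- **Statistical analyses, economic evaluation.** Means, standard deviations and 95% confidence intervals will describe differences in all relevant costs and outcomes, and the reader or decision maker is left to judge value.
- **Sample size and statistical power.** The trial is sized on appointments only: "26 patients in each group is required to identify a statistically significant reduction of at least one medical appointment between groups".

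The article gives no non-inferiority or equivalence margin, and no rule for judging a confidence interval.

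**The concern.** The hypothesis has two parts that need different kinds of evidence. The reduction in use and costs is a claim of difference, and a two-tailed test can support it. Comparable quality of life and satisfaction is a claim that any loss is too small to matter, and a test of no difference cannot support that. If the test is significant in the wrong direction, the claim is contradicted. If it is not significant, the data may fit no loss, a trivial loss or a material one.

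This part of the hypothesis is what makes a reduction in appointments acceptable to families and services. As the plan stands, a smaller, noisier or more incomplete dataset makes the result that fits the hypothesis more likely. That is the wrong incentive for a no-worse claim.

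**Working it through.** **1. The plan's own figure.** The sample size section gives "Accepting an alpha risk of < 0.05, a beta risk of < 0.2 and assuming a 10% risk of dropout during follow-up" and 26 per group for a difference of one appointment. Mean counts are not stated, so 26 cannot be derived from the stated inputs alone. If means of 2 and 1 are assumed, the two-sided square-root Poisson formula gives

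n = (1.96 + 0.84)² / [2(√2 − √1)²] = 22.9, so 23; and 23/0.9 = 25.6, so 26.

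The figure is therefore reachable, but for appointments. Nothing was sized on quality of life or satisfaction.

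**2. Evaluable children per arm.** 26 × 0.9 = 23.4, about 23. The abstract's total of 56 gives 28 × 0.9 = 25.2, about 25. I use 23 to 25.

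**3. Precision, unadjusted.** The article gives no SD for these outcomes, so results are in SD units. Half-width = t(0.975, 2n − 2) × √(2/n).

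- n = 23: 2.015 × 0.295 = 0.59 SD
- n = 25: 2.011 × 0.283 = 0.57 SD

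For illustration, with an assumed PedsQL SD of 15 (range 12 to 20) and 23 per arm, the half-width is 8.9 points (7.1 to 11.9).

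**4. Chance that a real deficit is non-significant.** The normal approximation is 1 − Φ(d/SE − 1.96), with SE = √(2/n) × √(1 − r²), where r is the assumed correlation with baseline (0 if unadjusted). The upper end of each range uses the t distribution.

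| True deficit | r | n = 23 | n = 25 |
|---|---|---|---|
| 0.5 SD | 0 | 60–62% | 58–59% |
| 0.5 SD | 0.5 | 50–52% | 47–48% |
| 0.5 SD | 0.6 | 44–46% | 40–42% |
| 0.3 SD | 0 | 83% | 82% |
| 0.3 SD | 0.6 | 75–76% | 74–75% |

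The rows with r above 0 can apply to PedsQL and EQ-5D-Y, which are collected at enrolment and at the end. The AFEQ and the Measure of Processes of Care are listed only at the end, so the r = 0 rows apply to them.

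**5. What a margin would demand.** The smallest margin that can be excluded with 80% power (one-sided 2.5%, true difference zero) is (1.96 + 0.84) × √(2/n).

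- n = 23: 2.80 × 0.295 = 0.83 SD
- n = 25: 2.80 × 0.283 = 0.79 SD

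For a margin of 0.5 SD, n = 2 × (2.80/0.5)² = 62.7, so 63 evaluable per arm, or 63/0.9 = 70 randomised per arm. With an assumed r of 0.5 the figures are 48 and 54. The margins are assumptions, since the article gives none.

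**The case against.** The strongest reply has five parts.

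- **Equivalence is not claimed from non-significance.** A reader might infer that the trial will treat a non-significant result as proof of equivalence. The article does not say so. It says the models estimate an effect, and it plans 95% intervals for the decision maker to weigh. This stands, and the stronger reading should not be made. The intervals are descriptive, though, and no threshold is set, so they do not turn the hypothesis into something the data can confirm.
- **Two-tailed testing at 5% is not wrong.** This also stands. It corresponds to the 95% interval that a non-inferiority comparison would use. What does not fit is a difference test standing alone behind a comparability hypothesis.
- **Improvement is also expected.** The economic paragraph anticipates improvements across outcomes that include quality of life and satisfaction, and a difference test suits that. The article is mixed on this, but the formal hypothesis in the Aims is comparability.
- **These are not the primary outcome.** The Discussion names service use and costs as primary, and leaving other outcomes unpowered is ordinary practice. This lowers the severity. It does not remove the mismatch.
- **A fuller protocol or SAP may hold a margin.** That is possible, and a missing margin alone would not be a finding. The point rests on what the article does state: a test framework for all outcomes that cannot answer one of its stated hypotheses.

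Baseline adjustment also weakens any claim that a 0.5 SD loss in PedsQL would usually be missed. At r = 0.6 it would be missed in fewer than half of trials.

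**Conclusion.** The mismatch is real. The Aims state a no-worse hypothesis for quality of life and satisfaction, the Statistical analyses section fixes tests of difference for all outcomes, and the planned intervals have no threshold. No planned result can confirm comparability.

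At 23 to 25 evaluable children per arm, losses of 0.3 to 0.5 SD would often go undetected. Unadjusted, a 0.5 SD loss is missed in about 58 to 62% of trials; with baseline adjustment for PedsQL this falls to about 40 to 52%. A 0.3 SD loss is missed in roughly 74 to 83% across these cases. The sizes rest on assumed deficits, correlations of 0.5 to 0.6 and the article's 10% dropout. The mismatch itself rests on none of them.

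Severity: SHOULD-FIX, because these outcomes are not primary and the planned intervals already supply most of the repair.

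**What to change.** Before data are seen, take one of two routes.

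1. **Margin route.** Name one key quality-of-life outcome (for example, caregiver-reported PedsQL total) and one satisfaction outcome, each with a justified margin. State that care is not compromised only if the two-sided 95% interval for the difference, adjusted for baseline where one exists, excludes a loss as large as the margin. Otherwise report the result as inconclusive. State the expected half-width of the interval.
2. **Estimation route.** If no margin can be justified, withdraw comparability and absence of compromise as testable hypotheses. Report each estimate with its 95% interval, and say that a non-significant difference is not evidence of comparability.

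Neither route needs more children or more data. Both need a protocol amendment with ethics approval, and a registry update if the change counts as major. The margin route also needs real work to justify the margins. At this sample size its conclusion on quality of life may well be inconclusive, since only margins of about 0.8 SD unadjusted could be excluded with 80% power.

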An economic evaluation will take the form of a cost-consequence analysis, where descriptive statistics including means, standard deviations and 95% confidence intervals will be used to summarise differences across all relevant cost and outcome measures between the two models of care. This type of economic evaluation design was chosen to reflect the nature of the intervention where improvements are expected to be seen across a range of health service and patient outcomes (including family out of pocket costs, health system costs, quality of life, patient experience, patient satisfaction, wait times). The cost-consequence analysis framework allows for any changes in these outcomes to be reported clearly and transparently without the restriction of needing to identify a single outcome measure of interest, as is the case with cost-effectiveness analysis. The reader or decision maker is then able to form an opinion about the value of this service change taking account of all relevant costs and outcomes. Specific cost categories to be reported on in the analysis will include allied health and specialist outpatient appointment costs, emergency department presentations, hospital admissions costs and costs of patient (family) travel and time off work to attend appointments. EQ-5D-Y responses will be converted to a utility score using an appropriate published value set. Utility scores will be reported separately for child self-completion and caregiver proxy completion questionnaires. These utility scores will then be used to generate estimates of Quality Adjusted Life Years (QALYs) for each treatment group.

As this study is registered on the ANZCTR and occurring within Metro North Hospital and Health Service, the trial may be randomly audited by an independent study monitor at any time point in the study. Given that this study is unblinded and not comparing rates of mortality or major morbidity, a data monitoring committee will not be set up for the purposes of this specific study.

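### Hospital adjustment is named only for quality of life and patient experience; the primary service-use and cost differences are given as descriptive summaries without a hospital term, which costs precision but not validity

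*Protocol article*

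**What the plan says.** Three places in the protocol article bear on this.

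- **Statistical analyses, first paragraph.** The modelling is introduced with the reason "To account for clustering at the hospital level and repeated measures over time". The same sentence names what is modelled: "multivariable mixed-effects regression models will be built to estimate the interventional effect of health related quality of life and patient experiences between and within groups". Service use and costs are not named there.
- **Statistical analyses, economic evaluation paragraph.** For the cost-consequence analysis, the stated method is: "descriptive statistics including means, standard deviations and 95% confidence intervals will be used to summarise differences across all relevant cost and outcome measures". No regression model and no hospital term is mentioned. The outcomes listed in that paragraph include quality of life and patient experience as well as costs.
- **Discussion.** "Data collected on health service use and costs, the primary outcome, will be obtained from administrative databases". This is the only place where a primary outcome is named. It fits the sample size section, which is built on the number of medical appointments.

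On allocation, the Randomisation section describes a blocked list and envelopes opened by clinic nurses at each site. It does not say whether the list is stratified by hospital.

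**The concern.** The plan gives its fuller analysis to the supporting outcomes and only a descriptive summary to the outcome it calls primary. Appointment counts and costs could plausibly differ between two hospitals through clinic organisation, unit costs or local booking habits, although the article gives no data on this. If they do differ, a hospital term would remove that variation from the comparison, and in a trial of 26 children per arm the gain could matter.

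There is also an ambiguity about the cost-consequence table. Quality of life and patient experience are to be estimated by model in one paragraph and summarised descriptively in the next. The article does not say which arm difference the decision maker will see in the table, and the two need not agree.

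**Working it through.** **Inputs from the article.** Two hospitals; children randomised individually, with equal arms intended; 26 per arm (Sample size and statistical power).

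**Inputs assumed.** The hospital difference D, in within-hospital SDs, is taken as 0, 0.5, 1 and 1.5. The split of children between hospitals is even unless stated. The article gives neither figure.

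**The plan's own figure.** The 26 per arm cannot be derived from the stated inputs, because no mean number of appointments is given. With assumed Poisson means of 2 and 1, two-sided 5% and 80% power, the square-root formula gives 7.849 / [2(√2 − √1)²] = 22.87, and 22.87 / 0.9 = 25.4, so 26. This only fixes the size used below. The precision ratios do not depend on it.

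**Step 1: variance.** With an even split, the variance within an arm is 1 + D²/4 when hospital is left out and 1 when it is in the model. The ratio of adjusted to unadjusted standard error is 1/√(1 + D²/4).

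| D | Variance, no hospital term | SE ratio | SE cut |
|---|---|---|---|
| 0 | 1.0000 | 1.000 | 0% |
| 0.5 | 1.0625 | 0.970 | 3% |
| 1 | 1.2500 | 0.894 | 11% |
| 1.5 | 1.5625 | 0.800 | 20% |

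**Step 2: are the unadjusted intervals valid?** This was simulated with 52 children, two hospitals, normal outcomes, no treatment effect and 8,000 runs per setting. A t interval was compared with a linear model containing a hospital term. Results for the even split:

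| Allocation within hospital | D | Coverage, unadjusted | Coverage, adjusted | Width, unadjusted | Width, adjusted |
|---|---|---|---|---|---|
| Balanced | 0 | 95.2% | 95.3% | 1.108 | 1.109 |
| Balanced | 0.5 | 95.7% | 95.2% | 1.143 | 1.108 |
| Balanced | 1 | 97.1% | 94.6% | 1.244 | 1.109 |
| Balanced | 1.5 | 98.7% | 94.8% | 1.395 | 1.108 |
| Not balanced | 0 | 95.0% | 95.2% | 1.106 | 1.118 |
| Not balanced | 0.5 | 95.0% | 95.0% | 1.143 | 1.119 |
| Not balanced | 1 | 95.1% | 94.8% | 1.242 | 1.121 |
| Not balanced | 1.5 | 95.2% | 94.9% | 1.393 | 1.122 |

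With about a 70:30 split, unadjusted coverage was 94.9% to 98.0% (balanced) and 94.6% to 95.1% (not balanced). Simulation error is about √(0.95 × 0.05 / 8000) = 0.24 percentage points, so no setting falls materially below 95%.

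When arms are balanced within each hospital, the hospital effect cancels from the arm difference but stays in the arm SDs, so the unadjusted interval is too wide. When they are not balanced, the interval has the right coverage on average but is wider than it need be.

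**Step 3: chance site imbalance, if allocation is not balanced by hospital.** The SD of the difference between arms in the share of children from one hospital is √(0.5/26) = 0.139. A difference of 15 points or more then has probability 2 × [1 − Φ(0.15/0.139)] = 0.28. The exact figure is 0.33 with binomial site totals, or 0.41 with 26 children fixed at each hospital. A 15-point imbalance shifts the unadjusted difference by 0.15 × D, which is 0.075, 0.150 and 0.225 SD at D = 0.5, 1 and 1.5. The standard error from within-hospital variation alone is √(2/26) = 0.277 SD.

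**The case against.** **The intervals are not wrong.** A reader might infer that leaving hospital out makes the cost intervals too narrow, as it would in a cluster-randomised trial. The documents do not support this. Children are the unit of randomisation, and the simulation shows nominal or higher coverage. This part of the objection stands in full.

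**The plan does not say that hospital must be handled for every outcome.** It gives clustering, together with repeated measures, as the reason for the quality-of-life and experience models only. That also stands. The point is uneven treatment, not a breach of the plan's own rule.

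**Costs may yet be modelled.** The modelling paragraph also says, without limiting it to quality of life, that "Continuous outcome measures will be analysed using linear regression models". Its statement on two-sided testing covers all outcomes. The economic paragraph does not call its summaries unadjusted or the only analysis, and a fuller analysis plan may exist. This stands in part. The general sentence leaves room for a cost model, but the only method tied by name to cost differences is the descriptive one. Appointments are treated as counts in the sample size section, and no count model appears in the list of models.

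**Two estimates for one outcome are not a contradiction.** Reporting a model estimate and a descriptive summary side by side is ordinary practice. That is fair. What is missing is a statement of which difference goes into the table.

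**The size is assumed.** Both sites are secondary public hospitals and nothing shows a gap of 1 SD or more. At D = 0.5 the gain is only 3%. The simulation used normal outcomes, whereas appointments are counts and costs are usually skewed. All of this stands and limits how strongly the point can be put.

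**Conclusion.** The point holds as a matter of precision and consistency. Hospital adjustment is named for the quality-of-life and experience outcomes but not for the primary one, whose stated method is descriptive. The unadjusted intervals are valid or too wide, so no claim of understated uncertainty or inflated false positives should be drawn from this.

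Under the assumed differences and an even split, the unadjusted comparison carries a standard error that a hospital term would reduce by about 3%, 11% or 20%. That corresponds to 6%, 25% or 56% more children analysed without adjustment. If allocation is not stratified by hospital, a chance imbalance in site shares also goes uncorrected. That does not affect coverage on average, but it can move the difference seen in this one trial. If the hospitals do not differ, nothing is gained. The change is worth making because it is cheap, not because the present method fails.

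**What to change.** In the economic evaluation paragraph of Statistical analyses, state that the arm differences in appointments and in costs, with their 95% confidence intervals, come from a regression on arm with hospital as a fixed term. A fixed term is preferable here because two hospitals are too few to estimate a random-effect variance. Report the result in appointments and dollars, by an identity link or by marginal standardisation from another link.

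Keep means and SDs per arm as description. For quality of life and patient experience, state that the differences in the cost-consequence table are the estimates from the mixed models already planned.

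The cost is a sentence or two, a little analysis time and one degree of freedom. In the simulated case with no hospital difference, the interval widened by about 1% at most (1.106 to 1.118). Adding age as a covariate is optional and not part of this point.
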